## Abstract

**Background:**

Pain is one of the most frequent and distressing symptoms in cancer patients. For the majority of the patients, sufficient pain relief can be obtained if adequate treatment is provided. However, pain remains often undertreated due to institutional, health care professional and patient related barriers. Patients self management skills are affected by the patients' knowledge, activities and attitude to pain management. This trial protocol is aimed to test the SCION-PAIN program, a multi modular structured intervention to improve self management in cancer patients with pain.

**Methods:**

240 patients with diagnosed malignancy and pain > 3 days and average pain ≥ 3/10 will participate in a cluster randomized trial on 18 wards in 2 German university hospitals. Patients from the intervention wards will receive, additionally to standard pain treatment, the SCION-PAIN program consisting of 3 modules: pharmacologic pain management, nonpharmacologic pain management and discharge management. The intervention will be conducted by specially trained oncology nurses and includes components of patient education, skills training and counseling to improve self care regarding pain management beginning with admission followed by booster session every 3rd day and one follow up telephone counseling within 2 to 3 days after discharge. Patients in the control group will receive standard care.

Primary endpoint is the group difference in patient related barriers to management of cancer pain (BQII), 7 days after discharge. Secondary endpoints are: pain intensity & interference, adherence, coping and HRQoL.

**Discussion:**

The study will determine if the acquired self management skills of the patients continue to be used after discharge from hospital. It is hypothesized that patients who receive the multi modular structured intervention will have less patient related barriers and a better self management of cancer pain.

**Trial Registration:**

ClinicalTrials NCT00779597

## Background

Pain is still one of the most frequent and distressing symptoms in cancer patients particularly in advanced stages of disease [1-3]. A currently published survey on symptom prevalence in more than 1300 cancer patients with various malignancies showed that almost 85% suffer from pain [4]. Pain was not only a frequent symptom but had also high intensity with a mean score of 5.0 (range 2.0 - 7.0 on a 0 to 10 NRS). Untreated and persistent pain interferes with patients' activities of daily living and reduces health related quality of life (HRQoL) [5].

For up to 90% of patients, sufficient pain relief can be obtained if adequate guideline based treatment is provided [6]. However, pain often remains undertreated due to patient related, institutional or health care professional barriers [7]. Therefore sufficient treatment of pain and associated symptoms must be based on receptive attitudes and effective self management of the patient, facilitated through patient education and counseling.

Patient related barriers include attitudes and believes about pain treatment in four dimensions: firstly misconceptions of physical effects of pain medication, such as that medication cannot really control pain, medication should be saved in case the pain gets worse or side effects of pain medication are difficult to control; secondly fatalism, e.g. the concerns that the pain treatment is ineffective; thirdly communication related barriers, e.g. not annoying the professionals by complaining about pain or distracting the physician from treating the disease by paying attention on pain treatment; fourthly worries about harmful effects of pain medication, e.g. that pain medication is very addictive. These attitudes and believes are held by almost all patients and build barriers for adequate pain control [13,16].

The evidence on psycho educational interventions to reduce patient related barriers is limited. Four RCTs have tested the effectiveness of such programs [8-11]. None of these trials implemented the intervention in an inpatient setting and two suffer from small sample size [8,11]. Furthermore, generalisability of these results to clinical settings is limited, due to a low degree of involvement of regular ward staff in application of study intervention, and application only in cancer subtypes (e.g. gynecological cancers).

Therefore the aim of this study is the evaluation of Self Care Improvement through Oncology Nursing, SCION-PAIN a multi modular nursing administered program. The program includes interventions to optimize pharmacological and nonpharmacological pain treatment, additionally to pain related discharge management and counseling to reduce patients' barriers and improve pain management. We will compare the effectiveness of the intervention on a trans institutional path, starting with an inpatient setting and continuing to home setting after discharge.

To avoid contamination, the intervention will be applied at the level of wards and the study is designed as a cluster randomized clinical trial.

## Methods

In two German university hospitals, eighteen inpatient wards with each at least 10% of patients diagnosed with cancer will be randomized. Patients will be included if they are aged 18 to 80 years, have a cancer diagnosis, an average pain intensity score of ≥ 3.0 (on a 0 to 10 NRS), pain persistence for more than 3 days, the ability to read, write, and understand German, a scheduled follow up appointment at the clinic, and signed written informed consent.

Patients will be excluded if they have a limited performance status (ECOG 4), documented ongoing alcohol or drug abuse, surgery within the last 3 days or showing disorientation regarding date, place and situation.

The study will be performed according to the ICH-GCP principles and was approved by the regional ethics committees of Martin-Luther-University Halle-Wittenberg and Technical University Munich.

### Interventions

The SCION-PAIN program is aimed to reduce patient related barriers to pain management in order to decrease pain intensity and pain interference with daily activities, as well as improving adherence and HRQoL. The program was developed by a part of the authors based on extensive literature review on efficient pain management. SCION-PAIN program includes three modular algorithm based protocols summarized in a handbook for the professionals, supplemented by a teaching booklet tailored to the patients' needs, a patient held record, a discharge self preparation checklist, and a compact disc with PMR exercise [12].

The intervention is structured into three modules. The first module "Pharmacologic pain management" addresses adequate pain assessment, effective communication about pain and administration of pain medication. The second module "Nonpharmacologic pain management" includes information about the effectiveness of complementary pain treatment methods and the application of a compact disc based PMR exercise. The third module "Pain related discharge management" provides advice on how to maintain the self management strategies learned in module one and two after discharge. Additionally, a checklist to ensure adequate discharge management is administered. This checklist contains seven essential questions to be answered during hospitalization, e.g. who will prescribe me further pain medication at home or who will provide advice in case of inappropriate pain management. The checklist will be assessed for completeness by the research nurse one day before discharge. The third module is aimed to prepare patients to detect possible situations of inappropriate self management and to counteract appropriately.

The content of all three modules is summarized for the patient within the 33-paged education booklet "Leave the pain behind you". Each pain related topic is specially enriched with information regarding patient related barriers to pain management, according to the domains identified by Ward [11] and Gunnarsdottir [13]. For example, a frequent patient related barrier is the reluctance to report pain in order to be a "good patient". Addressing this problem, patients get specific information about the importance of communicating pain in order to provide the best possible pain management. The booklet was developed by a part of the authors based on a literature review and approved by an institutional advisory panel of pain experts.

The administration of the modules will be individually planned for each patient in the intervention group depending on her or his educational needs. These demands will be assessed through a process documentation to ensure a homogenous intervention. The documentation will allocate the patients into one of three groups (low, intermediate and high resources for self management) consistent with their resources regarding knowledge, self care actions, and attitudes. Accordingly, each module can be fully, partially or not at all applied on the patient. The assessment of educational needs will be revised before and after every follow up counseling throughout the course of the intervention.

The first session will be held by the research nurse within 24 h after trial inclusion containing an overall introduction on self management of pain based on the booklet handed out to each patient (see figure 1).

**Figure 1 F1:**
[figure not shown]
**SCION-PAIN program intervention structure**.

Continuing the educational program the day after first education took place, the follow up sessions is going to be carried out by specially trained ward nurses. Unless the patient calls for further educational needs, the following counseling sessions will be scheduled every third day until patients' discharge or attainment of high resources for self management regarding knowledge, self care actions, and attitudes.

The intervention will end with a final obligatory application of a part of module three comprising a follow up telephone counseling carried out by the research nurse within 2 to 3 days after discharge. The counseling is based on a telephone guideline [14] and addresses additional issues to the previous session, as indicated in the process documentation.

Prior to the implementation, all modules were critically approved by an expert panel including nurses of the participating hospitals and scientific experts.

In the intervention group, the program will be administered by specially trained ward nurses in cooperation with a research nurse. Nurses will be trained in a 6 hours course on how to carry out the intervention. The training is going to be organized as interactive workshops and implemented through one to three "bed side" trainings at the ward. We refrained from administering the intervention program solely by research nurses because we want to assess our intervention in a pragmatic way and integrated in nurses' daily schedule.

Patients from the control group will receive standard care. Standard care includes standard pharmacological pain treatment, but neither standardized teaching or application of written materials, nor other evidence based treatment protocols are given.

### Outcomes

The effectiveness of SCION-PAIN program will be assessed by the following outcome measures at the individual patient level:

Primary outcome is the difference in patient related barriers to management of cancer pain (Barriers Questionnaire II) between control and intervention group [13].

The secondary outcome measures include:

1. intensity of pain (sensory dimension)

2. impact of pain and interference of pain in the patient's life (reactive dimension) [15]

3. Coping with pain [16]

4. Adherence to pain medication [17] and

5. HRQoL [18]

The outcome measures above will be assessed at trial inclusion, at discharge and 7, 14 and 28 days after discharge. The effectiveness of SCION-PAIN program will be assessed on an individual patient level by comparing the patient related barriers at day 7 after discharge in control versus intervention group.

### Sample size

Sample size was calculated based on the t-test (α = 0.05) for cluster randomized controlled studies [19] with an assumed clinically relevant difference of 0.4 points (SD 0,7) per BQ II item, an intra cluster correlation (ICC) of 0.05 and a power of 80%. These assumptions yield a sample size of 208 study participants. To allow some moderate drop out, 240 participants will be included into the study.

### Randomization

Participating wards will be pair matched before randomization according to their clinical profile. Randomization of wards will be performed (1) within these matched pairs, (2) concurrently for all wards prior to study, (3) by a reproducible SAS PROC PLAN code, and (4) by an external department (Institute for Medical Epidemiology, Biostatistics, and Informatics of the Martin-Luther-University Halle-Wittenberg). Thus, the allocation procedure on cluster and individual level will be concealed. The individual patients will be included according to their basic treatment of malignancies on the participating wards.

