### Statistical methods

The statistical analysis of the primary outcome patient related barriers to pain management will be conducted based on hierarchical models for the analysis of cluster randomized trials [19], including a random intercept for the respective ward. Due to our limited number of wards we a priori specified to statistically adjust the analysis by covariates (age, sex, diagnose, metastasis, performance status (ECOG), pain management/CPMI [21], pain duration, cancer treatment [22-24], depression and anxiety [7] that are significantly (P < 0.1) different at baseline. We plan to test baseline differences not routinely but because we expect significant baseline differences due to experience of previous CRT in a similar setting with 16 clusters where we found systematic and explainable differences between groups at baseline [25]. Baseline differences will be judged by simple t- and χ^2^-tests.

Subgroup analyses will be undertaken by checking interaction between well established covariates (anxiety, depression and pain intensity [7]) and primary outcome. An intention to treat approach will be used for the analysis. The trial will be reported according to the guidelines of the consolidated standards of reporting trials (CONSORT) extension for cluster randomized controlled trials [26].

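### The stated primary model has no term for hospital, although the 18 wards lie in two hospitals and clinical profile is the only matching criterion named

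*Protocol article*

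**What the plan says.** The Methods section sets the design: "In two German university hospitals, eighteen inpatient wards with each at least 10% of patients diagnosed with cancer will be randomized". The number of wards per hospital is not given.

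The Randomization section names one matching criterion: "Participating wards will be pair matched before randomization according to their clinical profile". It does not define clinical profile or mention hospital. It continues: "Randomization of wards will be performed (1) within these matched pairs". All wards were allocated together, before the study began.

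The Statistical methods section describes a hierarchical model for the primary outcome, "including a random intercept for the respective ward". Adjustment is for "covariates (age, sex, diagnose, metastasis, performance status (ECOG), pain management/CPMI [21], pain duration, cancer treatment [22-24], depression and anxiety [7", limited to those "that are significantly (P < 0.1) different at baseline". Every item on this list is a patient characteristic; hospital is not among them. The section gives the expectation of systematic baseline differences, based on an earlier 16-cluster trial, as the reason for this adjustment.

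**The concern.** Hospital is known before randomization, has only two levels and could plausibly affect the outcome. The control arm receives standard care, which may differ between two institutions. A plan that expects its arms to differ at baseline, and adjusts for that reason, would be expected to carry the site factor in its model. As described, the model does not.

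What is at stake depends on how the pairs were formed:

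- **Pairs that cross hospitals.** Randomization within such pairs does not balance hospital between arms. Part of any hospital difference then enters the treatment estimate, in whichever direction the allocation fell.
- **Pairs within a hospital.** Each hospital contributes equally to both arms and nothing is confounded. Without a hospital or pair term, however, the random ward intercept absorbs the hospital difference, and the standard error is larger than it need be.

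In the first case a pair term would not solve the problem, because hospital varies within each crossing pair.

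**Working it through.** **Inputs from the Sample size section.** Difference 0.4 points per BQ II item, SD 0.7, ICC 0.05, α = 0.05 (taken as two-sided), power 80%, 208 patients before drop-out and 240 after. From the Methods section: 18 wards, so 9 pairs and 9 wards per arm.

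**Inputs assumed.** The documents give no hospital difference, so H (points per item) is varied. They give no ward split, so an even 9/9 split is used where one is needed. Wards are taken as equal in size.

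**The plan's own figure.** 2 × (0.7 × (1.960 + 0.842) / 0.4)² = 48.07. Wards per arm with the small-number correction for pair matching: c = 2 + 48.07 × (1 + (m − 1) × 0.05) / m. At m = 13, c = 2 + 48.07 × 1.60 / 13 = 7.92, rounded up to 8. Then 2 × 8 × 13 = 208, as stated. The article does not give m, so the match rests on about 13 patients per ward.

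**Base precision, 208 patients in 18 wards.** m = 208/18 = 11.56.
- Ward variance: 0.05 × 0.49 = 0.0245. Patient variance: 0.4655.
- Variance of a ward mean: 0.0245 + 0.4655/11.56 = 0.0648.
- SE = √(2 × 0.0648 / 9) = 0.120. Power (noncentral t) is 87.9% on 16 df, and 87.6% on 15 df with a hospital term that is balanced across arms.

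**Case A: pairs cross hospitals.** Shift in the estimate = H × (hospital share in the intervention arm − hospital share in the control arm).
- One crossing pair: 5/9 − 4/9 = 1/9. At H = 0.3 the shift is 0.03 points. With a 9/9 ward split at least one pair must cross, because nine is odd.
- 6:3 split: 6/9 − 3/9 = 1/3. The shift is 0.07 at H = 0.2 and 0.10 at H = 0.3, against a target of 0.4.
- Probability of a 6:3 or more uneven split with a 9/9 ward split, by number of crossing pairs: 0% (one), 25% (three), 37.5% (five), 45% (seven), 51% (all nine; 260/512). A 7:2 or more uneven split has an 18% chance (92/512) if all nine cross.

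**Case B: pairs within hospital, no hospital term, ICC 0.05 applying within hospital.** An even split adds H²/4 to the ward variance.

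| H | Added variance | SE | Power without hospital | Power with hospital fitted |
|---|---|---|---|---|
| 0.1 | 0.0025 | 0.122 | 86.6% | 87.6% |
| 0.2 | 0.0100 | 0.129 | 83.0% | 87.6% |
| 0.3 | 0.0225 | 0.139 | 76.9% | 87.6% |
| 0.4 | 0.0400 | 0.153 | 69.2% | 87.6% |

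**Case C: ICC 0.05 already includes hospital differences.** The total ward variance stays at 0.0245 and power without a hospital term stays at 87.9%. Fitting hospital leaves 0.0245 − H²/4: 0.0145 at H = 0.2 (power 92.3%) and 0.0020 at H = 0.3 (97.1%). H = 0.4 is impossible here, since 0.0400 exceeds 0.0245.

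**Cost of the term when arms are unbalanced by hospital.** The SE is multiplied by 1/√(1 − r²), where r is the difference in shares. At 6:3, r = 1/3 and the factor is 1.06, so SE = 0.127 and power is 83.6%. The 87.6% therefore holds only for balanced hospitals.

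**The case against.** The strongest reply is that the article is silent rather than wrong. Clinical profile is undefined, and wards may have been paired within hospital. The model description reads as non-exhaustive and does not bar a site term; the covariate list concerns baseline variables screened by tests, and a design factor could be handled elsewhere. This stands against any claim that hospital was ignored in the matching or can never be adjusted for. It does not alter the model as written, which fixes the random effect, the covariates and the selection rule and contains no hospital term.

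A second reply is that the alarming figures come from extreme settings. This stands: 51% needs a 9/9 ward split with all nine pairs crossing, and the documents give neither. The power loss needs the planned ICC to apply within hospital, yet the Sample size section does not restrict it so. A hospital difference of 0.3 is three quarters of the target effect and has no support in the text.

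Third, CPMI and cancer treatment are on the covariate list and may capture some of the site difference in pain treatment, though only if they pass the baseline screen. The research nurse's first session and telephone call belong to the intervention arm, so differences between nurses there are variation in the effect, not a site difference confounded with arm.

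A reader might infer that the primary comparison is biased or its test invalid. The documents do not support that. Any confounding would be chance imbalance in the realised allocation, with no bias in expectation, and the random ward intercept carries hospital variance into the standard error.

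**Conclusion.** The point holds as one of precision and avoidable chance imbalance. The primary model as described omits a known two-level design factor, and the article does not say that the pairing dealt with it.

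The size cannot be fixed from the documents. With an even ward split, the shift runs from nothing (hospital balanced) through one ninth of the hospital difference (5:4) to one third (6:3), and larger only under less likely splits. On power, if ICC 0.05 is a within-hospital figure, the plan stays above its 80% target at a difference of 0.2 points and falls below it at 0.3. If the ICC already covers both hospitals, the planned power is intact and a hospital term can only be expected to help when the sites differ.

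It would go too far to conclude that hospital is confounded with arm in this trial: that requires knowing that pairs crossed hospitals and how the allocation fell, and the article reports neither.

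**What to change.** Add one sentence to the Statistical methods section: hospital enters the primary model as a fixed effect, whatever the baseline tests show. State there whether pairs were formed within hospital, and report the intervention effect for each hospital descriptively.

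The cost is one of about 16 degrees of freedom. With hospitals balanced across arms and no true site difference, power goes from 87.9% to 87.6%; an uneven allocation costs more, as shown for 6:3, and in return removes the shift. No new data are needed. Re-matching the wards is not proposed, because allocation preceded the study and recruitment began in October 2008.

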### Blinding

Nurses who administer the interventions and assess the outcomes might be aware of group allocation due to their participation in the training to manage the SCION-PAIN program. Patients are not informed about group assignment, but might be aware of it due to unmasking information from nurses. Therefore group allocation perception of included patients will be assessed at the end of trial 28th day after discharge.

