### Implementation

Adult cancer patients with persistent pain will be recruited by the nurses of the participating wards under the guidance of a research nurse. Participants will be included in the trial if they meet inclusion criteria and have signed informed consent (see Figure 2). To ensure the implementation of the intervention, quality audits will be conducted in the intervention groups in both study centers based on the guidelines of the Royal Collage of Nursing [20] and the German Network of Quality Assurance in Nursing Care. The audit will be based on (1) regular monitoring of the trained nurses' knowledge about the training module, and (2) on an additional comparison of nursing records with study documentation for 10% of all included patients.

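### Allocation is said to be concealed at the individual level, but the listed procedures conceal only the ward assignment, and those who recruit patients can foresee the arm

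*Protocol article*

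**What the plan says.** All statements are in the protocol article.

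- **Unit of allocation (Background, end):** "To avoid contamination, the intervention will be applied at the level of wards".
- **Timing (Randomization):** wards are randomised within matched pairs, "concurrently for all wards prior to study", by SAS code run in an external department.
- **Conclusion drawn (Randomization):** "Thus, the allocation procedure on cluster and individual level will be concealed".
- **Who recruits (Implementation):** "Adult cancer patients with persistent pain will be recruited by the nurses of the participating wards under the guidance of a research nurse".
- **Who delivers (Interventions):** "In the intervention group, the program will be administered by specially trained ward nurses in cooperation with a research nurse". Also: "The first session will be held by the research nurse within 24 h after trial inclusion".
- **Awareness (Blinding):** nurses who give the intervention and assess outcomes "might be aware of group allocation due to their participation in the training to manage the SCION-PAIN program".

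**The concern.** Allocation is concealed at the individual level when the person deciding whom to approach and enrol cannot foresee the arm that patient will join. In a cluster trial that recruits after the clusters are randomised, this is lost unless patients are identified beforehand or recruited by someone unaware of the cluster's arm. The article describes neither, yet presents individual-level concealment as a consequence of the ward randomisation.

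The primary outcome is the patient's own attitudes and beliefs about pain treatment (BQ-II). If intervention wards tended to enrol patients who are more receptive to education, the arms would differ on the outcome without any treatment effect. If they tended to enrol those with the greatest need for education, a real effect would be masked. The trial is to be reported under the CONSORT extension for cluster trials, so an incorrect concealment statement would pass into the report.

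**Working it through.** The claim rests on no figure, so the main check is logical. The arithmetic afterwards only illustrates size.

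**Does individual-level concealment follow from the listed features?**

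1. Pair matching, one-time randomisation of all wards, reproducible code and an external department prevent anyone from steering a ward into an arm. They support concealment of the ward assignment when it is made.
2. The ward determines the patient's arm (Background), and every ward has its arm before the first patient is recruited (Randomization). Each prospective patient's arm is therefore settled before the approach is made.
3. The recruiters are nurses of those wards, guided by a research nurse (Implementation). On intervention wards, trained ward nurses and a research nurse run the programme, and the research nurse opens it within 24 hours of inclusion (Interventions). The Blinding section allows that nurses may know the allocation.
4. No stated feature keeps the arm from the recruiter. The remark in Randomization that patients enter according to their cancer treatment concerns which ward they are on. Withholding the arm from patients is a matter of blinding. The audit in Implementation checks delivery of the programme, not enrolment.

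The conclusion holds for the cluster level and fails for the individual level.

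**Illustration of size**

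Inputs from Sample size and Methods: SD 0.7, ICC 0.05, N = 208, 18 wards, two-sided α taken as 0.05.

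- Mean cluster size: m = 208/18 = 11.56
- Design effect: DE = 1 + (m − 1) × ICC = 1 + 10.56 × 0.05 = 1.528
- Standard error of the difference: SE = SD × √(4 × DE/N) = 0.7 × √(4 × 1.528/208) = 0.120 points

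Assumption, not in the article: selection produces a spurious difference of b points at day 7. For example, a baseline shift of 0.2 SD (0.2 × 0.7 = 0.14 points) that carries over with correlation 0.5 gives b = 0.14 × 0.5 = 0.07. With no true effect, the rejection rate is P(|T| > t at 0.975), where T is noncentral t with noncentrality b/SE. Degrees of freedom are 16 (18 wards, two arms) or 8 (nine matched pairs).

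| b (points) | Share of the 0.4-point target | b/SE | 16 df | 8 df |
|---|---|---|---|---|
| 0 | 0% | 0 | 5% | 5% |
| 0.05 | 12.5% | 0.42 | 6.8% | 6.6% |
| 0.07 | 17.5% | 0.58 | 8.5% | 8.1% |
| 0.10 | 25% | 0.83 | 12.3% | 11.4% |

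A shift of the opposite sign would, where the intervention works, reduce power by pulling the estimate towards no effect.

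**The case against.** The strongest reply is that recruiting after ward allocation is common in cluster trials, and that this plan does not hide it: the Blinding section states that nurses may be aware. There are also mitigating features. Wards are matched on clinical profile, eligibility criteria are written down, patients are not told their group, and BQ-II is measured at inclusion, so a baseline imbalance would be visible. All of this is true and lowers the risk. None of it stops the recruiter from foreseeing the arm. The planned adjustment reaches only listed covariates that differ at P < 0.1, and that list contains neither baseline BQ-II nor receptiveness to education.

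It is also fair that screening logs, information sheets and enrolment rules are operational details that an article leaves to the full protocol. Their absence is not the fault here. The fault is the positive claim.

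Three stronger readings are tempting but not supported:

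- A reader might infer that the trained nurses themselves identify and consent the patients. The article says only that nurses of the wards recruit, does not say who takes consent, and describes training for the intervention group. The point does not need this inference, because the ward fixes the arm.
- A reader might take the remark in Statistical methods that in an earlier trial "we found systematic and explainable differences between groups at baseline" as evidence of selective recruitment. No cause is given, and randomising 16 clusters with different case mix could produce the same pattern.
- A reader might see the Discussion's praise of random allocation as a second false claim. It is a standard statement about randomisation and does not assert concealment at recruitment. It only needs a qualifier.

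**Conclusion.** The statement is wrong as written in one respect. Concealment at ward level is adequate; concealment at individual level is claimed but not provided by the design described. This follows from the article's own account of timing, unit of allocation and recruitment, and depends on no numerical assumption.

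The consequence is a risk of recruitment bias, not a demonstrated bias. Its size and direction are unknown. The figures of about 8.5% (16 df) or 8.1% (8 df) for a 0.07-point shift, and about 12% or 11% for 0.10 points, rest on assumed shifts and on the planned SD, ICC and sample size. They show that a modest shift would matter, not that one will occur. It would go beyond the documents to conclude that the trial will favour the intervention. The correction should be made, because it is cheap and affects how the result is reported.

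**What to change.** 1. In Randomization, remove the reference to the individual level, so that concealment is claimed for the ward assignment only, and state that those recruiting patients are not concealed from the arm.
2. In Discussion, beside the statement on random allocation, acknowledge the risk of recruitment bias after ward randomisation.
3. Screen consecutive admissions on all 18 wards against the same written criteria, with the same information sheet in both arms.
4. Keep a log for each ward of patients screened, eligible and consented, with reasons for non-enrolment, and report enrolment fractions by arm.

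Having the research nurse confirm eligibility would not restore concealment, because that role also delivers the first session and the telephone counselling. Steps 3 and 4 do not restore it either; they narrow the room for selection and make it visible.

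The cost is two wording changes and a short log kept by existing staff, a small administrative burden. Sample size and the analysis model are unaffected.
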